### Randomization and blinding

A random grouping method will be adopted. The SPSS 26.0 statistical software is used to randomly generate serial numbers and groups, and blind selection cards are made and put into envelopes (with no difference in appearance). Numbers are according to the inclusion sequence of the subjects, and corresponding experimental groups are entered according to the blind selection cards. Envelope administrators will not participate in this study, and the staff who generate the allocation sequence, enroll participants, and assign participants to interventions will be different ones without communication about the allocation. When patients are treated, the operators should follow the treatment assignment.

The study will be conducted in a double-blind method. Due to the particularity of the operation, the operators (participating doctors and physiotherapists) will not be blinded, but only the electrophysiological indicator collectors, scale evaluators, data recorders, statistical analysts, outcome assessors, and the included subjects are blinded. The operators are not involved in the design of the protocol; thus, they have no determination of the potential differences of each treatment method. They only need to ensure the protocols are followed accurately, so that the treatment and results will not be influenced even though they are unblinded.

### Measurement

*Patient demographics*: age, gender, BMI, course of disease, functional damage and serious underlying diseases, and date of admission.

*Healthy control demographics*: age, gender, BMI, once eyes-closed resting state EEG signals, and real-time sEMG signals.

*Treatment information*: enrollment time, treatment time, hospital discharge time, withdrawal time, problems in the treatment period, scale evaluation (MBI, CSS, FMA-U, MMT, and Brunnstrom), eyes-closed resting state EEG signals, and real-time sEMG signals [19].

*Follow-up*: dates of follow-up visit, adjuvant therapies, overall health status at and during follow-up (recovery condition of the upper limb, activity of daily living, fundamental diseases, drugs, death, loss of follow-up), and scale evaluation (MBI, CSS, FMA-U, MMT, and Brunnstrom). The follow-up staff will also be blinded.

The trial time enrollment schedule is estimated to be 6–8 months with a 3-month follow-up after the end of treatment. In 48 h after signing the informed consent, the patients will be randomly divided into groups according to the order in the clinic and then receive treatment after being evaluated (Table 3).

**Table 3 Tab3:** Schedule of study procedures

**Study period**	**Washout**	**Observation**	**Baseline**	**Treatment**			**Follow-up**	
Timepoint	≦7 days	3-7 days	0 day	1 day*	3 week◈	3 week^⊙^	1 month	3 month
**Patients**								
Informed consent	×							
Eligibility screening			×					
Patients’essential information			×					
Allocation			×					
Primary outcome								
sEMG			×	×	×	×		
EEG			×	×	×	×		
sEMG synergy-coherence analysis			×	×	×	×		
EEG power spectrum analysis			×	×	×	×		
Secondary outcomes								
MBI			×			×	×	×
CSS			×			×	×	×
FMA-U			×			×	×	×
MMT			×			×	×	×
Brunnstrom			×			×	×	×
**Healthy controls**								
Informed consent			×					
Eligibility screening			×					
Patients’ essential information			×					
Primary outcome								
sEMG			×					
EEG			×					
sEMG synergy-coherence analysis			×					
EEG power spectrum analysis			×					
Blinding assessment				×	×	×		
Adjuvant therapy				×	×	×	×	×
Adverse events				×	×	×	×	×

### Outcome measures

#### Primary outcome measures

The primary outcomes are real-time sEMG signals [20] and eyes-closed resting state EEG signals [21].

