##### Patients

Before and after the first and last treatment, the immediate alpha, beta, delta, and theta bands of the eyes-closed resting state EEG of patients in the two groups and ask the patients to do the “reaching and retrieving” gross motion, recording the real-time sEMG data of RMS (root mean square) and MF (median frequency). Data of the following are collected: biceps brachii (BB), triceps brachii (TB), extensor carpi radialis (ECR), brachioradialis (B), extensor digitorum (ED), and flexor carpi ulnaris (FCU) during the whole process of the motion. Computer software calculates iEMG (integrated
electromyogram) and MPF (mean power frequency) values.

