##### Sample size estimation

Sample size estimation was carried out according to the study objectives and protocol, and the difference between RMS values of sEMG of BB was obtained from the pretest of group 1 and group 2 after treatment and the healthy group. The difference between the healthy group and group 1 was 167.61 and 68.17 for group 2, and the standard deviations were respectively 127.22 and 148.46. The study effect size is 0.8, *α* = 0.05, test efficiency 1 − *β* = 0.80, and the number of sample groups is two. The sample size of each group is 25, and the total sample size is 50. Considering the possibility of sample loss in the trial, the sample size should be increased by 20%. Finally, the total sample size of this study should be 60 and divided into two groups with 30 sample size for each group.

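### The primary outcome is two whole signal types (at least 28 variables at three post-baseline recordings), while alpha and power are set for biceps brachii RMS alone

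*Protocol article*

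**What the plan says.** Under Primary outcome measures the protocol article states: "The primary outcomes are real-time sEMG signals [20] and eyes-closed resting state EEG signals [21". No variable, muscle, frequency band, time or contrast is singled out.

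The Patients paragraph that follows gives the content and the timing:

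- EEG: "Before and after the first and last treatment, the immediate alpha, beta, delta, and theta bands of the eyes-closed resting state EEG", so four bands. Channels or regions are not given.
- sEMG as recorded: "recording the real-time sEMG data of RMS (root mean square) and MF (median frequency").
- sEMG as derived: "Computer software calculates iEMG" and, continuing the same sentence, "electromyogram) and MPF (mean power frequency) values".
- Muscles: six (BB, TB, ECR, B, ED and FCU).

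Table 3 agrees on the timing, with one baseline and three later columns for sEMG and EEG. Under the primary outcome it also carries a row for "sEMG synergy-coherence analysis" and one for EEG power spectrum analysis. The outcome section does not mention synergy-coherence.

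Sample size estimation uses one variable only: "the difference between RMS values of sEMG of BB was obtained from the pretest", for the two groups after treatment and the healthy group. It takes an effect size of 0.8, alpha 0.05 and power 0.80, which gives 25 per group and 60 in total after a 20% increase.

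Data statistical analysis prescribes paired tests within groups, and ANOVA with LSD (Dunnett's T3 if variances differ) or rank tests between groups. It ranks no outcome as primary, fixes no primary time or contrast, and mentions no adjustment across variables or times.

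**The concern.** The error rates claimed in the sample-size paragraph belong to one variable at one time. The label of primary outcome covers at least 28 variables at three times, and biceps RMS is nowhere called primary. LSD and T3 compare groups within one outcome, so they give no protection across outcomes or recordings.

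A nominally significant difference in any of the listed variables could therefore be reported as a primary finding, chosen after the results are seen, and no single result would carry the stated 0.05. This matters because the article's abstract expects the trial to verify efficacy and to support wide use of the therapy.

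**Working it through.** **Step 1: reproduce the plan's figure.** Inputs from Sample size estimation: effect size 0.8, alpha 0.05, power 0.80. Sidedness is not stated; two-sided is taken here.

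n per group = 2 × (1.960 + 0.842)² / 0.8² = 24.5, rounded up to 25. The t-based solution is 25.5, so 26. Total 2 × 25 = 50, and 50 × 1.2 = 60. The stated 25, 50 and 60 reproduce as a calculation for a single comparison at 0.05.

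**Step 2: count the primary family.** Inputs from the Patients paragraph:

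- sEMG: 6 muscles × 4 parameters = 24
- EEG: 4 bands
- Variables: 24 + 4 = 28
- Recordings: 4, less 1 baseline = 3
- Variable-by-time comparisons of PES with CES: 28 × 3 = 84

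The count is a minimum. It leaves out EEG channels, any synergy-coherence measures, within-group tests and contrasts with healthy controls.

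**Step 3: chance of at least one false positive.** Assumptions: no true difference, and each PES versus CES comparison tested on its own at two-sided 0.05, with no gate from the overall ANOVA.

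If independent, the chance is 1 − 0.95^m:

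- m = 28: 1 − 0.95^28 = 0.762
- m = 84: 1 − 0.95^84 = 0.987

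The documents give no correlations, so a range is assumed. With a common correlation ρ, the test statistics are Z_j = √ρ·W + √(1−ρ)·e_j, with W and e_j independent standard normal. The result is the share of 100,000 simulated trials in which any |Z_j| exceeds 1.96.

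| Assumed common correlation | 28 variables | 84 comparisons |
|---|---|---|
| 0 (exact formula) | 0.762 | 0.987 |
| 0.3 | 0.640 | 0.915 |
| 0.5 | 0.490 | 0.739 |
| 0.7 | 0.331 | 0.475 |
| 0.9 | 0.168 | 0.214 |

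**Step 4: a structured check.** RMS and iEMG both measure amplitude, and MF and MPF both summarise the spectrum, so each pair should be close to duplicate. Assumed correlations: 0.90–0.95 within each pair, 0.2 between amplitude and frequency measures, 0.3–0.8 between muscles, 0.3–0.5 between EEG bands, none between sEMG and EEG, and 0.6–0.9 between times. Across four such scenarios the chance is 42–62% for 28 variables and 60–90% for 84 comparisons.

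**Step 5: could the whole family stay primary?** With Bonferroni at effect size 0.8:

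- 28 tests: alpha 0.05/28 = 0.00179. About 50 per group are needed (52 t-based). Power is 33% at 25 per group and 44% at 30.
- 84 tests: alpha 0.05/84 = 0.000595. About 58 per group are needed (61 t-based). Power is 22% at 25 per group and 31% at 30.

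The planned size cannot support the family, but it was calculated for one endpoint.

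**The case against.** The best defence is that this is a condensed article and that multiplicity rules are commonly left to a statistical analysis plan, which is not shown. That stands as far as it goes: the absence of an adjustment is not in itself an error here. It does not answer the point. The article itself makes whole signal types primary and itself ties alpha and power to one variable. An adjustment written elsewhere would leave that mismatch in place, and Step 5 shows that adjusting the full family would cost most of the power.

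Several stronger readings are tempting and are not supported:

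- *That a false-positive primary result is more likely than not.* This depends on correlation. At a common correlation of 0.5 the figure for 28 variables is just under one half, and at 0.7 even all 84 comparisons stay below one half.
- *That 76% and 99% are lower bounds.* They assume independence, and positive correlation lowers them. Only the count of tests is a minimum.
- *That the article prescribes testing each variable at 0.05, or counts any single significant variable as success.* The analysis section gives no level, and no success rule is written. The 0.05 is taken from the sample-size paragraph because it is the only alpha stated.
- *That synergy-coherence is a further primary outcome.* Table 3 lists it beside EEG power spectrum analysis, so it may be processing of the listed sEMG signal. It is a mismatch of wording to be settled, and it is not in the count.
- *That the recording before the last session should be primary, because a post-session recording mixes lasting change with the immediate effect.* The two recordings do answer different questions, but the sizing refers to RMS after treatment, and the outcome text describes the EEG recordings as immediate. Preferring the pre-session recording is a matter of taste and does not correct an error.

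**Conclusion.** The point holds in this form: the protocol fixes no single primary variable, time or contrast, while its stated alpha and power apply only to biceps brachii RMS after treatment. If each PES versus CES comparison is tested at 0.05, the chance of at least one false-positive primary result runs from 17% (common correlation 0.9) to 76% (independence) for 28 variables, and from 21% to 99% for all 84 comparisons. These figures rest on assumed correlations and on a significance level carried over from the sample-size paragraph. The conclusion does not depend on the choice within that range: even at 0.9 the rate is 3 to 4 times the nominal 5% (0.168/0.05 = 3.4; 0.214/0.05 = 4.3). It should be put right before the results are read.

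**What to change.** Name one primary endpoint: biceps brachii RMS at the end-of-treatment recording, PES versus CES, tested at two-sided 0.05. State which recording is meant, so that it matches the after-treatment value used for sizing. Make the other sEMG parameters, the other five muscles, the EEG bands and the other recording times secondary or exploratory, with Holm or false-discovery-rate control. Align the primary-outcome rows of Table 3 with this, and say whether synergy-coherence is an outcome or a processing step.

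With one endpoint, the type I error for the primary claim is 0.05, and the planned 25 per group stands at the assumed effect size of 0.8. (Whether 0.8 follows from the pretest values is a separate matter: (167.61 − 68.17) / 138.25 = 0.72, where 138.25 pools the two stated standard deviations.)

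The change is to wording and needs no new data or patients. Its price is that the other sEMG and EEG variables can no longer be called primary results. The article reports that recruitment began on 3 June 2022 and was expected to last 2 months, and it was published on 11 May 2023. The documents do not show whether the change can still precede unblinding, so the date of the decision and the state of blinding should be recorded with it.

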##### Patients

Before and after the first and last treatment, the immediate alpha, beta, delta, and theta bands of the eyes-closed resting state EEG of patients in the two groups and ask the patients to do the “reaching and retrieving” gross motion, recording the real-time sEMG data of RMS (root mean square) and MF (median frequency). Data of the following are collected: biceps brachii (BB), triceps brachii (TB), extensor carpi radialis (ECR), brachioradialis (B), extensor digitorum (ED), and flexor carpi ulnaris (FCU) during the whole process of the motion. Computer software calculates iEMG (integrated
electromyogram) and MPF (mean power frequency) values.

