## Methods

### Pre-design

Five healthy subjects and five patients are selected to conduct a survey on the comfort of this instrument parameters, body position, stimulation time, muscle fatigue, completion of programmed movements, and other conditions and to refine the trial design in response to feedback and comments from participants.

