### Study design

This clinical trial is designed as a double-blind RCT with 90 participants (60 stroke patients and 30 healthy controls) to be recruited. SPIRIT checklist and CONSORT statement were used when writing this study protocol [13, 14]. The whole study duration is about 17 weeks, including the washout period (7 days), the screening observation (3–7 days), the treatment period (3 weeks), and the follow-up period (3 months) (Fig. 1). After signing the informed consent (version date: 2021.11.19, version number: V1.1), all patients will be randomized divided into two groups in a blind manner—programmed flexor–extensor alternating electrical acupoint stimulation group (PES group) and conventional flexor–extensor alternating electrical acupoint stimulation group (CES group) with 30 cases in each, and the treatment will last for 3 weeks (6 days of treatment with 1-day rest per week). Healthy controls are used as a baseline without treatment. Participation in the trial is entirely voluntary, and they can withdraw at any time during the study without any reason. The participants are blinded, and the signal acquisition, evaluation, and outcome assessors are blinded. Because the treatment operation is too programmed, it is difficult to blind the performers. To prevent unblinding, subjects are advised not to discuss treatment options with evaluators (Figs. 2 and 3). All the patients will be followed up for 3 months. The follow-up time points will be at the end of the 1st month and 3rd month after the trial. The data and results will be monitored by the Data and Safety Monitoring Committee (DSMC) and the Ethics Committee.

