##### Healthy controls

Before the beginning of the whole clinical trial, the immediate alpha, beta, delta, and theta bands of the eyes-closed resting state EEG of the healthy controls in a quiet, without any interference laboratory will be recorded and ask them to do the “reaching and retrieving” gross movement, recording the real-time sEMG parameters (RMS and MF) of BB, TB, ECR, B, ED, and FCU during the whole process of the motion. The computer software calculates iEMG and MPF values.

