##### Data statistical analysis

The SPSS 26.0 statistical software will be used for analysis by three-party statisticians. Data presentation: each measurement is presented as mean ± standard deviation if it conforms to a normal distribution, or median and quartiles if it does not. Intra-group comparisons: if the measurement data in each group conforms to a normal distribution, paired *T* test will be used for comparison between each group before and after treatment; if all data does not conform to a normal distribution, paired sample Wilcoxon rank sum test is used. Inter-group comparison: If the measurement data of conforms to a normal distribution, one-way ANOVA will be performed, and the LSD method will be used for comparison between the groups (Welch’s test will be used to correct Dunnett’s T3 method when the variance is not equal); if the data does not all conform to a normal distribution, non-parametric test will be performed (Mann–Whitney *U* method is applied for comparison between two groups, and Kruskal–Wallis *H* method is for comparison between multiple groups).

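### The plan does not fix which 3-week EEG/sEMG reading is compared; the likelier one, after the last session, mixes any short-lived session effect with the 3-week effect

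*Protocol article*

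**What the plan says.** Under primary outcome measures for patients, the EEG bands and the sEMG parameters are recorded "Before and after the first and last treatment, the immediate alpha, beta, delta, and theta bands". Table 3 agrees: sEMG and EEG are marked at baseline, at day 1 and in two separate 3-week columns. They are not marked at the 1-month or 3-month follow-up. The five clinical scales are marked at baseline, in the second 3-week column only, and at both follow-up visits.

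The data statistical analysis section describes the within-group comparison as "paired *T* test will be used for comparison between each group before and after treatment". Between groups it plans a one-way ANOVA with LSD comparisons, or non-parametric tests, and mentions no baseline adjustment. The sample size estimation uses biceps brachii "RMS values of sEMG of BB was obtained from the pretest of group 1 and group 2 after treatment and the healthy group". Neither section says whether the 3-week value is the one before or the one after the last session.

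**The concern.** The aim is upper limb functional reconstruction over a 3-week course, which is an effect meant to outlast a single session. A reading taken after the last session contains that effect plus whatever the session has just done to the muscle or the brain signal. The two 3-week readings therefore measure different things, and the stated comparison fits either.

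An acute effect that differs between arms cannot be ruled out, because the arms differ in how a session drives the muscles: in sequence in the PES group, synchronously in the CES group. The protocol's Pre-design survey of the instrument covers "stimulation time, muscle fatigue, completion of programmed movements", so fatigue was at least thought relevant to a session. A difference in short-lived after-effects could then be read as a difference in recovery, or could hide one. Because EEG and sEMG are not repeated at follow-up, no later primary reading could settle which it was.

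**Working it through.** **Which reading is likelier**

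1. Four moments are named for the primary signals, and Table 3 has four marked columns for them. In order, these are before the first session, after the first, before the last, and after the last.
2. The secondary outcomes section has the scales assessed before and after the whole trial. In Table 3 their end-of-treatment mark stands only in the second 3-week column.
3. That column is therefore the end-of-treatment assessment and, by the order in step 1, the one after the last session. This is an inference. The column symbols are not explained in the text at hand, and no weight is placed on that.

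**What each reading contains**

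Let θ be an arm's 3-week effect and a its acute effect from the last session, with P for PES and C for CES.

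- Between arms, post-session reading: (θ_P − θ_C) + (a_P − a_C). The second bracket vanishes if a_P = a_C.
- Within an arm, reading before the first session against reading after the last: θ + a. An equal acute effect in the two arms does not cancel here.
- Against healthy controls, who receive no stimulation: the patients' mean is shifted by a and the controls' is not.
- Reading before the last session: free of a. With 3 weeks × 6 treatment days = 18 days, and assuming one session per day, it follows 17 of 18 sessions.

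**The plan's own figure**

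The stated inputs are effect size 0.8, α = 0.05 and power 0.80; two-sided testing is assumed. The normal formula is n = 2(1.960 + 0.842)²/0.8² = 24.5, so 25 per group, as stated (an exact t test gives 25.5, so 26). Then 50 × 1.2 = 60, as stated.

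**Size of the possible distortion (assumed values)**

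The documents give no acute effect. As a share of the stated planning effect:

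- 0.1/0.8 = 12.5%
- 0.2/0.8 = 25%
- 0.3/0.8 = 37.5%

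The consequence for a two-sided t test with 25 evaluable per arm depends on the total difference L + a, where L is the lasting difference and a is now the arm difference in acute effect, both in SD units. The noncentrality is (L + a)·√(25/2) = 3.536(L + a), on 48 degrees of freedom.

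| L | a | L + a | Probability of significance |
|---|---|---|---|
| 0 | 0 | 0 | 5.0% |
| 0 | 0.2 | 0.2 | 10.7% |
| 0 | 0.4 | 0.4 | 28.3% |
| 0.8 | −0.4 | 0.4 | 28.3% |
| 0.8 | −0.2 | 0.6 | 54.7% |
| 0.8 | 0 | 0.8 | 79.1% |
| 0.8 | 0.2 | 1.0 | 93.4% |
| 0.8 | 0.4 | 1.2 | 98.6% |

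**The case against.** A reader might infer that the plan has chosen a value taken straight after stimulation, and that an uncontaminated alternative lies unused. The documents do not support that.

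- No section says that the 3-week comparison uses the post-session reading. Study design uses the word treatment for the whole 3-week course.
- No interval between the end of a session and the reading is given. The word immediate does not supply one: the healthy controls section uses it for people who receive no stimulation ("the immediate alpha, beta, delta, and theta bands of the eyes-closed resting state EEG of the healthy controls").
- The sample size sentence describes a pilot, and when the pilot reading was taken relative to a session is unknown.
- The reading before the last session is free only of that session's effect. Sessions run six days a week alongside rehabilitation and acupuncture, so the previous session may be only a day old.
- Pre-design mentions fatigue in a survey of comfort and parameters. It does not say that fatigue affects the sEMG or EEG values.
- Acupoints, treatment time and course are the same in both arms, and nothing shows that acute effects differ.

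All of this stands, and it limits the point to an unfixed timepoint with a conditional bias.

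Two further arguments carry less weight. One is that the four readings already allow acute and cumulative effects to be separated, with lasting function covered by the scales at 1 and 3 months. The readings do allow it, but the stated comparison does not use them that way, and the scales are secondary outcomes. The other is that the choice of contrast belongs in an analysis plan that is not shown. Mere silence would not be a finding. Here, however, the article states the endpoint and the tests in terms that fit two different values.

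**Conclusion.** The point holds as an ambiguity in the primary comparison, not as a demonstrated wrong choice. Two 3-week readings exist, the plan does not name which is compared, and the schedule makes the post-session one the likelier. If that one is used, acute and 3-week effects are mixed, with no primary reading at follow-up to separate them.

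Bias between arms requires unequal acute effects; with equal ones the contrast is unbiased. The within-group tests and any comparison with healthy controls are affected by any nonzero acute effect, equal or not.

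The size is unknown. The range of 12.5% to 37.5% of the planning effect rests on an assumed arm difference of 0.1 to 0.3 SD. The table also assumes a common SD and 25 evaluable patients per arm. It shows what would follow from such a difference, not that there is one. The change is worth making because it costs so little.

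**What to change.** In the primary outcome and analysis sections, name the reading before the last session as the 3-week primary value for EEG and sEMG. Compare the arms on it with adjustment for the reading before the first session, in place of the unadjusted one-way ANOVA. Use the same pair of readings for the within-group tests, and the same 3-week reading for any comparison with healthy controls. Report the after-minus-before change within the first and within the last session separately, as the immediate effect.

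This costs wording only, since every reading is already scheduled. There are three small downsides. The named reading leaves out the last session's contribution (one of 18 if sessions are daily). It may follow the previous session by only a day, so some carry-over can remain. The pilot SDs may not apply exactly to it, so the planning SD becomes approximate. No new sample size follows, because the documents give no SD for this reading and no correlation with baseline.
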